### Treatment of Non-compliance and Missing Data

We will follow enrolled patients until study end. We will analyze study outcomes according to original randomization scheme in an intent-to-treat approach. In case of missing data due to irreconcilable loss to follow-up, we will perform primary analyses using all available data with a regression-based multiple imputation procedure implemented in PROC MIXED and PROC MI in SAS software as per the SAS Institute (82). To evaluate sensitivity to systematic patterns of missingness, we will iterate multiple imputations by shifting or scaling the imputed values based on dropout models and comparing with estimated parameters. We will regard models to be “sensitive” if imputed values alter parameters by ≥15%.

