### Power and Sample Size for the Primary Outcome

The trial is powered for the primary outcome, MDS UPDRS-IV total score. A differential effect size of *d* = 0.89 in the change of OFF-time for PDAE vs. walking using data collected by Uc et al. (30) was observed (Table 1) (30).

Given the study design's 3- and 16-month timepoints, we will use Holm's procedure (62) to control for multiple testing. The alpha levels will be 0.025 and 0.05 for *p*-values in ascending order for comparing PDAE and WALK in the changes from the baseline at 3 and 16 months. The observed effect size (*d* = 0.89) is from participants that finished their programs in the shorter duration pilot studies; therefore, we expect the intent-to-treat effect size will be reduced. Thus, we power the study for an attenuated effect of the observed effect: *d* = 0.7, which is 64% of the observed effect size in our pilot study or 79% of the estimated effect vs. walking, giving us 81 and 88% power for the comparisons at alpha level of 0.025 and 0.05, respectively. With a sample size of *n* = 41 completers per group, total *n* = 82, we additionally expect to have medium to high (60–80%) power to detect differences between the PDAE and WALK groups on the visuospatial outcome (Aim 2), given that the estimated effect size for Corsi Blocks is 0.76 vs. a cognitively engaging contact control (63). We will assume 25% attrition and will therefore recruit 102 participants with PD. For the exploratory variables, we will only focus on effect estimation instead of inference testing given that we do not know the effect size.

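### The 15% rule for sensitivity to missing data describes stability of the estimate and is not anchored to the Holm decision, so it can pass a contrast whose conclusion is lost

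*Protocol article*

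**What the plan says.** The section on treatment of non-compliance and missing data (Protocol article) sets out three steps.

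- **Primary handling:** "we will perform primary analyses using all available data with a regression-based multiple imputation procedure".
- **Sensitivity analysis:** "we will iterate multiple imputations by shifting or scaling the imputed values based on dropout models and comparing with estimated parameters".
- **Criterion:** models are regarded as sensitive "if imputed values alter parameters by ≥15" percent or more.

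The section does not identify the parameters, explain the choice of 15%, or say what follows from the label.

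The primary conclusion is reached by a different route. Under Analyses, Aim 1, a significant group-by-time interaction opens the two PDAE versus WALK comparisons of change from baseline, at 3 and at 16 months. These are tested by Holm's procedure. The power section gives the levels: "The alpha levels will be 0.025 and 0.05 for *p*-values in ascending order".

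**The concern.** The sensitivity analysis exists because dropout may be informative, and the protocol assumes 25% attrition, so the rule is likely to be used. A reader will take the label *not sensitive* to mean that the PDAE versus WALK conclusion stands up to departures from the imputation model. The rule does not test that. A relative change depends on the size of the estimate it is divided by, and the cut-off makes no reference to the standard error, the confidence interval or the Holm levels.

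Two consequences follow. A borderline contrast can lose its Holm decision after a change below 15%, and a clear one can be flagged while its decision is secure. Because the parameters are not named, a near-zero coefficient in the mixed model (group, time, interaction, possible covariates) could also trigger the label after a trivial move.

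**Working it through.** **Inputs.** From the power section of the Protocol article: "41 completers per group, total" 82; design effect d = 0.7; alpha 0.025 and 0.05. Assumptions: two-sided tests (sidedness is not stated), a two-sample t comparison with 80 df in place of the mixed model, and a standard error that does not change when imputed values are shifted.

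**Step 1: reproduce the plan's figure.** SE(d) = √(2/41) = 0.221. The noncentral t with 80 df and d = 0.7 gives power of 81.0% at alpha 0.025 and 87.9% at 0.05. The article states 81% and 88%, so this simple set-up matches the one behind the plan.

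**Step 2: smallest significant estimate.** Critical d = t(1 − α/2, 80 df) × 0.221, which is 0.505 at alpha 0.025 and 0.440 at alpha 0.05.

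**Step 3: estimates that lose significance after a fall of less than 15%.** The range runs from critical d to critical d / 0.85.

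- alpha 0.025: 0.505 to 0.594
- alpha 0.05: 0.440 to 0.517

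**Step 4: examples.** p is two-sided from t = d / 0.221.

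| Estimate | Change | New estimate | p before | p after | Label under the rule | Decision |
|---|---|---|---|---|---|---|
| 0.55 | −10% | 0.495 | 0.015 | 0.028 | not sensitive | lost at 0.025 |
| 0.48 | −10% | 0.432 | 0.033 | 0.054 | not sensitive | lost at 0.05 |
| 0.70 | −15% | 0.595 | 0.002 | 0.009 | sensitive | kept at both levels |
| 0.10 | −20% | 0.080 | 0.65 | 0.72 | sensitive | non-significant throughout |

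The first two rows depend on the other time point. Row 1 is a lost Holm decision when the other contrast has not passed 0.025; if it has, 0.028 is compared with 0.05 and passes. Row 2 counts only when the other contrast has passed 0.025, because otherwise p = 0.033 was never a rejection. Both rows also presuppose a significant interaction. Row 3 needs no condition on the other time point.

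**Step 5: distance from the design value.** From d = 0.70, significance is lost after a fall of 1 − 0.505/0.70 = 28% (alpha 0.025) or 1 − 0.440/0.70 = 37% (alpha 0.05).

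**Step 6: how often an estimate is borderline.** If the true d is 0.7, the estimate falls in the Step 3 range with probability about 13% (alpha 0.025) or 8% (alpha 0.05). This is the chance of being exposed to the problem. Mislabelling also needs a fall that is large enough yet below 15%.

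**Step 7: the same rule expressed as a shift.** Suppose 25% of one arm is imputed and only that arm is shifted by δ SD. Then d moves by 0.25δ, and the flag is reached at δ = 0.15d / 0.25 = 0.6d.

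- At d = 0.10 the flag is reached at 0.06 SD.
- At d = 0.70 the flag is reached at 0.42 SD. The decision is lost only at (0.700 − 0.505)/0.25 = 0.78 SD (alpha 0.025) or (0.700 − 0.440)/0.25 = 1.04 SD (alpha 0.05).

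**The case against.** The strongest reply is that this is a change-in-estimate criterion and should be judged as one. It asks whether the estimate depends on the missing-data assumption, and on those terms calling a fall from 0.70 to 0.595 sensitive is correct. **This stands.** A reader might infer that the rule is unrelated to the conclusion, or that its labels are simply wrong in both directions. The document does not support either reading: a larger relative fall does lower the test statistic, and stability of the estimate is a legitimate thing to report. What fails is using it as the only criterion.

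A second reply is that the section attaches no consequence to the label and does not prevent adjusted estimates, intervals or p-values from being reported. **This also stands.** It would go too far to say that the rule decides how the primary result is reported.

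Third, the calculation is simplified. The planned model has three time points with multiple imputation. A 25% loss from 102 would leave about 38 per arm (102 × 0.75 / 2), not 41. The shift figures assume one arm only, whereas equal shifts in two arms with similar dropout would largely cancel. **These points limit the exact figures**, but they do not tie the cut-off to the Holm decision. From the design value the rule also flags early, which is the cautious direction.

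Fourth, such detail might be left to an analysis plan. **That does not apply to the cut-off itself**, because the article states the number. Step sizes and table layout can be left.

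**Conclusion.** The point holds as a badly fixed rule, and it should be corrected. The only stated criterion for sensitivity to missing data is a relative change of 15% or more in unnamed parameters. At the trial's own 41 per arm it can leave unflagged a contrast whose Holm decision is lost (0.55 to 0.495, p from 0.015 to 0.028) and can flag one whose decision is secure (0.70 to 0.595, p = 0.009). It is also unstable near zero.

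The size is moderate. Exposure is confined to borderline estimates, with about a 13% or 8% chance of landing there if the true d is 0.7. A reader might infer that the type I error of the primary test is affected. It is not: the label leaves that test unchanged, and the harm is a robustness statement that can mislead. The figures rest on two-sided tests, a t comparison with fixed standard error, the stated condition on the other time point, and a significant interaction.

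**What to change.** Keep the planned shifted and scaled imputations and amend the criterion, before unblinded data are seen:

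1. State that it applies to the PDAE versus WALK contrasts in change from baseline at 3 and 16 months.
2. Keep the 15% change only as a description of estimate stability.
3. Judge robustness of the conclusion by reporting, under each shift, the estimate, its confidence interval and the Holm decision.
4. Report the smallest shift at which the Holm decision changes, including shifts applied to PDAE only, and set it against the observed change in WALK and its SD.

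The cost is a few sentences of wording and slightly more analysis, with no new data, visits or participants. The downside is that the plausibility of the tipping shift is a judgement rather than a fixed cut-off. It is, however, a judgement the reader can see and check.

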## Discussion

Most people with PD experience OFF-time that severely impacts QOL (83–85). Little research has explicitly looked at the potentially synergistic relationship between the patient experience of drug efficacy and exercise therapies. We will provide insight into the beneficial outcomes of treatments like PDAE, in concert with best practice pharmacological treatment. Based on promising data, this trial will provide longitudinal short- and long-term effects of an evidence-based training to inform clinicians of the relationship between effective treatment and their pharmacological regimens. The patient experience of drug efficacy is multifactorial, involving confluence of biochemical pathway processes, motor and cognitive status, and social situations (14, 86–91). If our prediction is correct, reduced OFF-time could result from enhanced aerobic fitness, psychosocial engagement, or motor–cognitive skill enhancement via the therapy. Exercise may allow participants treated with levodopa to use dopamine more efficiently and improve motor symptoms (54, 88, 92). These beneficial effects may be reflected in better patient experience of drug efficacy. Recent evidence supports that AE involving motor skills differentially affects frontal–striatal-related circuits more than pure AE (22).

Combined physical/cognitive trainings done either simultaneously or in a tight series, e.g., stationary bicycling while completing computerized cognitive training on a screen, may benefit motor and cognitive function in humans, based on animal literature and some well-designed human studies (93–95). Spatial memory has been shown to improve with aerobic and resistance training exercises (96). Our own research has shown that Adapted Tango improves disease severity, balance, spatial cognition, and executive function (56). OFF-time is directly related to dopamine replacement therapy. Although the relationship between aerobic exercise and spatial cognitive function among PD patients with OFF-time is unclear, since exercise attenuates the levodopa-induced medication-related motor complications (88), improves incidental sequence learning (97), and improves visual memory and visuospatial abilities (98), it stands to reason that the exercise-dependent improvement in OFF-time may further improve spatial cognitive function.

In PDAE, physical and cognitive activities are solidly and seamlessly integrated. This project will reveal whether PDAE is efficient for spatial cognitive rehabilitation. If so, an advantage of PDAE is that it is more engaging and enjoyable than an alternative, e.g., computerized cognitive training done with exercise. We hypothesize that PDAE will rehabilitate spatial cognition in PD. We explain our reasoning here. During PDAE, one can learn coordinated relationships between people, places, and objects and one performs spatial navigation with a partner and other individuals. PDAE also requires strong cognitive engagement in several domains: attention to partner; storing new steps in memory and recalling previously learned steps; detecting and interpreting musical beats; coordinating body movement with external musical source and partner; and using working memory via learning steps and practicing them and language, via a new vocabulary for a dance context stringing together steps into phrases, and holding “conversations” with partner, via non-verbal communication. We expect positive effects of the AE component of PDAE on symptoms (30); however, the WALK group controls for aerobic exercise to isolate the cognitive elements inherent to PDAE. Correlations with improved non-trained spatial tasks suggest transfer effects of PDAE (99). Cognitive training for people with PD has induced long-term effects in brain activation (18 months post) (100). The cognitive elements of PDAE would rehabilitate cognition similarly over the long term. Furthermore, cardiovascular fitness modulates brain activation associated with spatial learning (101). We plan to uncover neural mechanisms of benefit to cognitive domains via fMRI.

We propose that the social support/human touch and cognitive engagement inherent to PDAE will benefit participants more in OFF-time and in cognitive function. It has not been unequivocally demonstrated that any form of exercise can slow neurodegeneration in humans although aerobic exercise has been demonstrated to slow neurodegeneration in animal models (86). As such, we propose using PDAE as a model in humans, given PDAE's replicated beneficial effects in multiple studies (53, 92, 102). Exercise has been touted as neuroprotective in humans based on findings in rodent studies; however, evidence is needed within humans to firmly establish exercise as neuroprotective. PDAE evidently benefits motor and cognitive function and may improve drug efficacy; with better understanding of neurodegenerative processes after the course of long-term intervention, novel, and more effective therapies can be developed. A potential neuroprotective effect of PDAE might be reflected in reduced iron accumulation and slowed NM loss. Furthermore, the evidence of a correlation between cognitive benefits and neural activity in brain regions anatomically referable to these cognitive functions suggests a relationship between slowed neurodegeneration and the cognitive impact of PDAE, which might exceed that of WALK. Given the previous benefits seen with exercise modalities, and specifically with PDAE, it is reasonable to expect some impact upon the neurodegenerative process, which can be robustly and rigorously characterized with our biomarkers.

The therapeutic benefits of dance have been studied since the 1900s and have produced interesting findings; however, additional clinical trials are necessary to strengthen the evidence in support of partnered dance treatment for people with PD.

## Data Availability Statement

The raw data supporting the conclusions of this article will be made available by the authors, without reservation, upon request.

## Ethics Statement

This study has been approved by both the Emory IRB and the VA Research and Development committees. Written informed consent will be obtained from all participants prior to participation.
